### Statistical methods

#### Missing data

Although we have internal quality control methods to ensure data integrity, follow-up nonresponse shall be an inescapable challenge in a prospective observation study. Fortunately, we will recruit experienced physicians with stable patient population (at least 5 years of acupuncture experience or middle and senior titles), so the bias for lack of follow-up could be controlled partially. Real-time monitoring of the electronic network platform shall control missing data less than 20%. According to the classical rules of missing classification, follow-up nonresponse belongs to missing not at random (MNAR) [40]. Multiple imputation invented by Rubin shall be adopted to process missing data [41].

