#### Effective rate

Minimal clinically important difference (MCID) is an index to identify effective group, that is the NRS score decreased by 2 points or ODI score cut down 10 points [36]. The effective number divides the total number of people included in the analysis is the effective rate.

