### Sample size

Currently, there is no valid sample size calculation method for registry studies. According to experience, the principle of sample size estimation in multivariate analysis of variance is 5–10 times the number of variables. Our preliminary research variables are no more than 20, so the sample size of the study is 1000–2000, taking the maximum value, our sample size is set at not less than 2000. To ensure better data representation and reflect the diversity of acupuncture operations, we will recruit no less than 9 centers, at least 3 acupuncturists in each center, that is, at least 27 acupuncturists.

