#### Analytic approach

Data with poor compliance, non-compliance with the study program or missing important information are not included in the analysis. Data processing and statistical analysis will use SPSS version 24 (IBM Corp., Armonk, NY, USA) and SAS Version 9.4 (SAS Institute Inc., NC 27513–2414, USA).

We will select 1-week,4-week,12-week, assessments respectively at evaluation time point on the ODI and NRS index. Firstly, baseline characteristics comparability needs to be assessed between the propensity-matched groups. Model adjustment suggested by Rosenbaum and Rubin will be adopted to conquer residual covariance imbalances [42]. Secondly, multivariate linear regression models will be employed to adjust the propensity score and baseline characteristics. Once matched, change in ODI and NRS between-group at different observation points will be calculated by paired t-test. Thirdly, logistic regression models will be used to evaluate the magnitude of impacts contributed by baseline factors on acupuncture effectiveness for CLBP patients. Descriptive analysis will be used for variables such as the recruited research center,s basic characteristics of doctors and patients, initial diagnosis and intervention details. Quantitative data (Height, Weight, NRS, ODI, etc.) will be described by mean, standard deviation, median, maximum and minimum values. The enumeration data (Acupuncture style, Acupoint selection principle, Operation of acupoints, Effective rate etc.) and ranked data (Educational background, Physician title) will be described by numbers, percentages, rate and constituent ratio. If necessary, parametric methods or alternate nonparametric methods will be selected appropriately.

We will adopt the propensity score matching of patients at 1:1 to imitate an RCT. Baseline confounder will be equilibrated and matched on variables such as demographic data, medical history, duration, intensity, back function. The comparative analysis will be conducted after the baseline unevenness adjustment. Propensity score will match comparison group, such as Traditional Chinese acupuncture style vs Microacupuncture style (Scalp acupuncture, Ear acupuncture, Wrist and ankle acupuncture, Eye acupuncture, Umbilical acupuncture, Abdomen acupuncture), Local acupoint selection vs Non-local acupoint selection and Single Acupuncture vs Combined therapy etc.

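### Follow-up non-response is declared missing not at random, then handled by multiple imputation with no non-ignorable model named, so the stated remedy does not fit the stated mechanism

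*Protocol article*

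**What the plan says.** Under Missing data, the protocol article expects follow-up non-response and classifies its mechanism outright: "According to the classical rules of missing classification, follow-up nonresponse belongs to missing not at random (MNAR"). The next sentence gives the remedy: "Multiple imputation invented by Rubin shall be adopted to process missing data". The same paragraph offers two reassurances. Recruiting experienced physicians with stable patient populations should partly control the bias, and "Real-time monitoring of the electronic network platform shall control missing data less than 20" per cent.

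Under Analytic approach a second rule touches the same data: "Data with poor compliance, non-compliance with the study program or missing important information are not included in the analysis".

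The outcomes concerned are the primary ones. NRS and ODI are scheduled at the first visit, the last visit and each follow-up contact (Table 2). The effective rate is derived from them, counting a patient as a success when "the NRS score decreased by 2 points or ODI score cut down 10 points". Its denominator is the number of people in the analysis.

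**The concern.** Multiple imputation as usually implemented fills in a missing score from the distribution seen in respondents who share the same observed data. That is the MAR assumption. MNAR means that, given the observed data, non-respondents still differ from respondents. The article asserts MNAR and then adopts a method whose default form assumes that no such difference exists. It names no non-ignorable model that would reconcile the two.

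The classification itself is too firm. No rule assigns follow-up non-response to MNAR. The mechanism depends on why patients stop responding and on what was recorded about them, and it cannot be confirmed from observed data.

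The exclusion rule adds a second conflict. Table 1 marks NRS, ODI and effective rate as indispensable items, so a patient without a follow-up score can be read as missing important information. One section would impute that patient and the other would drop the same patient. Dropping does not correct MNAR either.

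At stake are the size of the primary results and the honesty of their intervals. In a registry of this size the intervals will be narrow, so even a small bias matters for coverage.

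**Working it through.** The plan states no figure that depends on this point, so there is nothing to reproduce. The statements are compared first, and the possible size is illustrated after that.

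**Statements side by side**

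| Place | Statement | What it implies |
|---|---|---|
| Missing data | Follow-up non-response is MNAR | Observed data do not fully explain the difference between missing and observed scores |
| Missing data, next sentence | Rubin's multiple imputation, no model named | As ordinarily run, observed data do fully explain it (MAR) |
| Analytic approach | Records missing important information are left out | Such patients are dropped, not imputed |

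**Inputs from the article**
- Missing fraction f: the 20% ceiling (Missing data).
- MCIDs: 2 NRS points and 10 ODI points (Effective rate).
- Sample size: at least 2000 (Sample size).

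**Assumed input**
- δ is the true mean score of the missing patients minus the mean that MAR imputation predicts for them. The article gives no value, so a range is used. Its sign is unknown.

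**Overall mean.** The absolute bias is f × |δ|.
- NRS: 0.20 × 0.5 = 0.1; 0.20 × 1 = 0.2; 0.20 × 2 = 0.4 points.
- ODI: 0.20 × 2.5 = 0.5; 0.20 × 5 = 1.0; 0.20 × 10 = 2.0 points.

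**Matched-group comparison.** The absolute bias is |f_A δ_A − f_B δ_B|.
- Loss 20% and 10%, δ = 2 NRS points in both: 0.4 − 0.2 = 0.2 points.
- Loss 20% and 10%, δ = 10 ODI points in both: 2.0 − 1.0 = 1.0 point.
- Loss 20% in both, δ = 2 NRS points in one group and 0 in the other: 0.4 − 0 = 0.4 points.
- Equal loss and equal δ: 0.

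**Interval coverage.** A simulation used n = 2000, 20% missing, MAR-based normal imputation on baseline with 20 imputations, and 200 replicates. The baseline-outcome correlation of 0.5 and the missingness slopes are assumptions.

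| Log-odds of being missing, per SD of the unseen score | Bias of the mean (SD) | Coverage of the 95% interval |
|---|---|---|
| 0 (not MNAR) | about 0 | 0.97 |
| 0.5 | −0.07 | 0.14 |
| 1.0 | −0.14 | 0.00 |

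The minus sign follows from letting worse scores go missing more often. Reversing the slope reverses the sign.

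A hand check agrees. The standard error is about √(0.75/1600 + 0.25/2000) = √0.000594 = 0.0244 SD. A bias of 0.074 SD is then 0.074/0.0244 = 3.0 standard errors, which leaves coverage of about 0.14.

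**Effect of the exclusion rule on the effective rate.** With 2000 patients and 20% missing, 0.20 × 2000 = 400 patients are affected. Imputation keeps the denominator at 2000. Exclusion reduces it to 1600.

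**The case against.** The strongest reply has three parts.

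First, multiple imputation is a framework and not a MAR model. It can carry non-ignorable models, and a condensed article may leave the imputation model and sensitivity analyses to a fuller document. This stands in part: the absence of those details is no finding. But the article does state both a mechanism and a remedy, and as written they do not match. A fuller document could supply a suitable model, yet the published pairing and the over-firm classification would still need correcting.

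Second, the shifts are small. Even a full MCID of unexplained difference at the 20% ceiling moves an overall mean by one fifth of the MCID (0.4 of 2, or 2 of 10). Matched comparisons may be affected less or not at all, and the article already concedes selection bias and unknown confounding. This stands for the size in points. It does not protect interval coverage for cohort-wide estimates.

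Third, a reader might infer that the results will be biased toward benefit. The documents do not support this. They do not say that non-respondents do worse, and recovered patients may also stop responding.

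A reader might also put a number on the effective rate, for example 60% in respondents falling to 54–57% overall if non-respondents achieve 30–45%. Those inputs are invented, and the sum measures the bias of analysing respondents only. Imputation also conditions on observed scores, including those at the last visit, and can absorb the part of the gap that they predict.

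**Conclusion.** The point holds. The article declares MNAR and adopts multiple imputation without naming a model suited to MNAR. On its own premise, the imputed primary results could be biased in an unknown direction, with intervals that do not show it. The assertion of MNAR by rule is itself unsound, and the exclusion of records missing important information is not reconciled with imputation.

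It would go too far to say that imputation is the only handling stated, because the exclusion rule is a second one, though it is no remedy for MNAR.

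Under the assumed departures, the size is 0.2 to 0.4 NRS points or 2 ODI points in an overall mean at 20% missing. For matched groups it is the difference of the two products of loss and departure. The coverage figures rest on an assumed correlation and slopes, ignore clustering by centre and acupuncturist (which would widen the intervals), and concern a mean over the whole cohort. They do not carry over directly to the matched comparisons.

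**What to change.** 1. Under Missing data, say that follow-up non-response *may be* MNAR, in place of *belongs to*.
2. State the working assumption of the main multiple imputation: MAR given recorded baseline and treatment-period data, namely baseline and last-visit NRS and ODI, number of sessions, centre and acupuncturist. Follow-up disease status should not be relied on as a predictor. It is collected at the same contacts as the scores and will usually be missing with them.
3. Add a delta-adjusted (pattern-mixture) sensitivity analysis. Shift the imputed scores separately by comparison group and in both directions, up to the plan's own MCIDs (2 NRS points, 10 ODI points). Re-derive the effective rate from the shifted scores, and report the delta at which each conclusion changes.
4. Under Analytic approach, define which missing information leads to exclusion, so that patients who lack only follow-up outcomes are imputed and stay in the denominator.

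If a fuller analysis plan already contains such an analysis, the article needs only to say so and to correct the mechanism statement and the exclusion rule. The cost is a few lines of text and some extra runs in SAS 9.4, which the article already names. No new data are needed.

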#### Analytic approach

Data with poor compliance, non-compliance with the study program or missing important information are not included in the analysis. Data processing and statistical analysis will use SPSS version 24 (IBM Corp., Armonk, NY, USA) and SAS Version 9.4 (SAS Institute Inc., NC 27513–2414, USA).

We will select 1-week,4-week,12-week, assessments respectively at evaluation time point on the ODI and NRS index. Firstly, baseline characteristics comparability needs to be assessed between the propensity-matched groups. Model adjustment suggested by Rosenbaum and Rubin will be adopted to conquer residual covariance imbalances [42]. Secondly, multivariate linear regression models will be employed to adjust the propensity score and baseline characteristics. Once matched, change in ODI and NRS between-group at different observation points will be calculated by paired t-test. Thirdly, logistic regression models will be used to evaluate the magnitude of impacts contributed by baseline factors on acupuncture effectiveness for CLBP patients. Descriptive analysis will be used for variables such as the recruited research center,s basic characteristics of doctors and patients, initial diagnosis and intervention details. Quantitative data (Height, Weight, NRS, ODI, etc.) will be described by mean, standard deviation, median, maximum and minimum values. The enumeration data (Acupuncture style, Acupoint selection principle, Operation of acupoints, Effective rate etc.) and ranked data (Educational background, Physician title) will be described by numbers, percentages, rate and constituent ratio. If necessary, parametric methods or alternate nonparametric methods will be selected appropriately.

We will adopt the propensity score matching of patients at 1:1 to imitate an RCT. Baseline confounder will be equilibrated and matched on variables such as demographic data, medical history, duration, intensity, back function. The comparative analysis will be conducted after the baseline unevenness adjustment. Propensity score will match comparison group, such as Traditional Chinese acupuncture style vs Microacupuncture style (Scalp acupuncture, Ear acupuncture, Wrist and ankle acupuncture, Eye acupuncture, Umbilical acupuncture, Abdomen acupuncture), Local acupoint selection vs Non-local acupoint selection and Single Acupuncture vs Combined therapy etc.

Hierarchical models based on the pain grading, medical center, age group, gender, TCM syndromes and classification of diseases will be taken into account to explore the important factors affecting the effectiveness of acupuncture for CLBP [43–45]. Conditional logistic regression models adjusting by different variables to identify predictors of long-term effectiveness presented by ODI and NRS or recurrence at the12-week follow-up.

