**Methods:**

A prospective, multi-center and dynamic registry study. All acupuncture related information will be collected through a high-quality structured network platform. Patients with CLBP included in the study met the following criteria: age from 16 to 80 years, using acupuncture as a main therapy and voluntarily signing the informed consent. At least 2000 patients, 27 acupuncturist, and 9 medical centers will be recruited under actual clinical settings at the first stage. Numeric rating scale (NRS), Oswestry Disability Index (ODI) and Effective rate will be measured in pain and functional disability assessment, respectively, as the primary outcome. Evaluation index will be collected at the baseline and follow-up in 1, 4, 12 weeks after the last visit. Hierarchical models and regression analysis will be used to explore the key factors affecting acupuncture effectiveness. Effects between propensity matching groups (Traditional Chinese acupuncture style vs Microacupuncture style, Local acupoint selection vs Non-local acupoint selection, Single Acupuncture vs Combined therapy) will be compared.

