CLBP information	✓	✓	✓	✓	✓				
Diagnosis	✓								
Lumbar imaging	✓								
Informed Consent	✓								
Acupuncture rationale	✓								
Acupuncture details	✓	✓	✓	✓	✓				
Acupuncture regimen	✓								
Combined therapy	✓	✓	✓	✓	✓				
Numerical Rating scale (NRS)	✓				✓	✓	✓	✓	
Oswestry Disability Index (ODI)	✓				✓	✓	✓	✓	
Adverse event	✓	✓	✓	✓	✓	✓	✓	✓	
Disease status						✓	✓	✓	✓

^a^The number of acupuncture treatments shall be no less than three times, ^b^No less than three follow-up visits

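### The analysis set, and with it the effective-rate denominator, depends on post-enrolment compliance and completeness, and the exclusion rule is not reconciled with the imputation plan

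*Protocol article*

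**What the plan says.** - **Exclusion rule (Statistical methods, Analytic approach):** "Data with poor compliance, non-compliance with the study program or missing important information are not included in the analysis". The article gives no threshold for poor compliance and does not confine the rule to a secondary analysis.
- **Denominator (Outcome measures, Effective rate):** "The effective number divides the total number of people included in the analysis is the effective rate". A patient counts as effective on the criterion "that is the NRS score decreased by 2 points or ODI score cut down 10 points".
- **Status of the outcome (Abstract, Methods):** "Numeric rating scale (NRS), Oswestry Disability Index (ODI) and Effective rate will be measured in pain and functional disability assessment, respectively, as the primary outcome". The paragraph under Primary outcomes names only NRS and ODI, but Effective rate is described before the secondary indicator.
- **Missing data:** follow-up nonresponse is classed as missing not at random (MNAR), the target is under 20% missing, and "Multiple imputation invented by Rubin shall be adopted to process missing data".
- **Table 2 footnotes:** "The number of acupuncture treatments shall be no less than three times" and "No less than three follow-up visits". They belong to a data-collection timetable and do not mention the analysis set.

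**The concern.** Compliance and completeness of outcome data are known only after treatment has begun. A denominator that depends on them describes the patients who stayed and were fully recorded, not the patients who were treated. The registry enrols consecutive patients to limit selection bias, and the Discussion promises to characterise patients for whom acupuncture does not work. An exclusion at the analysis stage can bring selection back and remove some of those patients.

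Two further matters depend on the same sentence. The propensity-matched comparisons (acupuncture style, acupoint selection, single versus combined therapy) balance baseline variables only, so matching cannot correct exclusions that occur at different rates by regimen after treatment starts. And with one rule that drops records lacking important information and another that imputes missing data, two analysts following the article could report different primary results.

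**Working it through.** **Inputs.** The article states no expected effective rate, no expected share excluded and no response rate among the excluded, so there is no figure of its own to reproduce on this point. The under-20% target covers missing data only; exclusions for poor compliance would come on top. All rates below are therefore assumptions. Only the planned minimum of 2000 patients comes from the article.

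**Formula.** Let e be the share excluded, pR the effective rate among those analysed and pE the rate among those excluded.

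- All-patient rate = (1 − e) × pR + e × pE
- Bias of the reported rate = pR − all-patient rate = e × (pR − pE)

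The sign is that of pR − pE. As pE runs from 0 to 1, the bias runs from +e × pR to −e × (1 − pR), a span equal to e.

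**Main example: e = 20%, pR = 60%** (400 of 2000 excluded, 1600 analysed).

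| pE | All-patient rate | Bias, points |
|---|---|---|
| 0% | 0.8 × 60 + 0.2 × 0 = 48% | +12 |
| 30% | 0.8 × 60 + 0.2 × 30 = 54% | +6 |
| 60% | 0.8 × 60 + 0.2 × 60 = 60% | 0 |
| 80% | 0.8 × 60 + 0.2 × 80 = 64% | −4 |
| 100% | 0.8 × 60 + 0.2 × 100 = 68% | −8 |

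**Range over other assumptions (extremes of pE).**

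| e | pR | Bias, points |
|---|---|---|
| 5% | 60% | +3 to −2 |
| 10% | 60% | +6 to −4 |
| 20% | 50% | +10 to −10 |
| 20% | 70% | +14 to −6 |
| 30% | 60% | +18 to −12 |

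**Regimen comparison.** Suppose two regimens both show 60% among those analysed and 30% among those excluded, but one loses 10% and the other 30%. Their all-patient rates are 0.9 × 60 + 0.1 × 30 = 57% and 0.7 × 60 + 0.3 × 30 = 51%. The analysed sets show no difference, while the treated patients differ by 6 points.

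**The two rules side by side.** The Missing data section speaks of follow-up nonresponse and imputes it. Analytic approach drops records lacking important information and does not define the term. Table 1 marks NRS and ODI as indispensable, so a missing score can be read as missing important information. On that reading the record is dropped; under the Missing data section it is imputed. Nothing in the article gives one rule precedence.

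**The case against.** The strongest reply is that the two rules can coexist. The imputation section is about follow-up nonresponse, while the exclusion may be aimed at unusable baseline or treatment records; Data monitoring uses similar language for registry-entry problems. That is a possible reading, so a flat contradiction is not proven. The ambiguity over a missing NRS or ODI stands, as does the separate exclusion for compliance, which imputation does not touch.

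A second reply is that Participant timeline provides for telephone follow-up of patients who do not come back, so early stoppers are not simply lost. This may reduce missing data. It does not exempt a contacted patient from being dropped for poor compliance.

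A third is that compliance thresholds and analysis-set definitions usually sit in a full protocol or SAP, which is not shown. That is fair for the thresholds, and their absence is not the point. The point is a rule the article states outright, together with a denominator that inherits it.

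A reader might also infer more than the text supports:

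- **That patients with fewer than three sessions are excluded.** The minimum is a timetable footnote. It becomes an exclusion only if falling short counts as non-compliance with the programme, which the article does not say. The same holds for the minimum of three follow-up visits.
- **That early adverse events are hidden.** Adverse events are recorded from the first visit onward and serious ones are to be reported promptly. No section says that safety uses the filtered set.

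**Conclusion.** The concern holds as a stated rule that leaves a primary outcome open to selection bias of unknown size and sign. It is tempting to conclude that the effective rate is biased upward. That follows only if excluded patients respond less often than those kept, which is plausible when patients leave for lack of benefit but is not shown. Patients who improve early may also stop attending or skip follow-up, and they would push the bias downward. With an assumed 20% excluded and 60% effective among those analysed, the range is +12 to −8 points; at 5% excluded it narrows to +3 to −2. The protocol's own MNAR classification implies that nonresponders may differ in ways tied to outcome, so the exclusion cannot be assumed harmless.

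The boundary with the imputation plan and the standing of the Table 2 minimums are unresolved in the text. This should be fixed before analysis. No stated figure is shown to be wrong.

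**What to change.** 1. Replace the exclusion sentence in Analytic approach with a primary analysis set: all eligible, consented patients with a baseline NRS and ODI and at least one acupuncture session, regardless of compliance or number of sessions.
2. Use that set as the denominator of the effective rate.
3. State that missing follow-up NRS and ODI are imputed under the Missing data section, so that one rule governs them.
4. Add an MNAR sensitivity analysis, for example counting patients with missing outcomes as not effective. Standard multiple imputation assumes data missing at random, so on the protocol's own MNAR premise it would not by itself remove the bias.
5. State that the Table 2 minimums do not determine membership of the primary set.
6. State that safety is summarised in all patients with at least one session.
7. Keep the compliant set as a labelled sensitivity analysis, with its definition and the number excluded by reason and by regimen.

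The cost is analysis wording and keeping records that are already entered. The downside is more imputed values and possibly a lower headline effective rate.

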### Participant timeline

As a dynamic registry design, we plan to stick to the registry for at least 2 to 5 years. The tolerance range of time is 3 days around the follow-up point. If the patient does not return after the last visit, follow-up is done by phone within 1 week. At least ensure follow-up at these three time points,1 week, 4 weeks and 12 weeks. Contents of follow-up: whether there is a recurrence, whether there is back pain related surgery, whether there is any other treatment.

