	CLBP Information	Indispensable	Visit date, Chief complaint, Course of disease, Location of pain, Characteristics of pain, causes of pain aggravation, Medical history, Causes of pain relief, Back function, Concomitant symptoms, History of acupuncture and Reception, auxiliary examination
	Diagnosis information	Indispensable	Disease diagnosis, Syndrome differentiation of TCM etiology and meridians, Complicating disease
	Lumbar imaging	Optional	X ray, CT examination, Magnetic Resonance Imaging
	Informed Consent	Indispensable	NA
Acupuncture treatment process	Acupuncture rationale	Indispensable	Acupuncture date, Acupuncture style, Acupoint selection principle, Operation of acupoints
	Acupuncture details	Indispensable	Response elicited, Needle retention time, Needle stimulation, Needle type (gauge, length), Adjunctive therapy, Needle parameter, Co-intervention
	Acupuncture regimen	Indispensable	Number of treatment session, Frequency of treatment
	Combined therapy	Indispensable	Pharmacotherapy, Non-pharmaceutical therapy, Other acupuncture type
Outcomes	Effectiveness evaluation	Indispensable	NRS, ODI, Effective Rate
	Safety evaluation	Indispensable	Adverse events
	Follow up	Indispensable	Disease status (Recurrence, Lower back pain related surgery, Seeking other treatments)

*CT* Computed tomography, *NA* Not applicable, *NRS* Numeric rating scale, *ODI* Oswestry disability index, *TCM* Traditional Chinese Medicine

Considering the characteristics and clinical practice of acupuncture therapies, we referenced Standards for Reporting Interventions in Clinical Trials of Acupuncture (STRICTA) [27] to building data dictionaries and frameworks. Structured, standardized, and logical metadata will be accumulated to reflect the real clinical process of acupuncture treatment for CLBP. Baseline demographic data, CLBP characteristics, patient-centered outcomes of the effectiveness and safety will be truthfully recorded. Specific data element entry and minimum dataset in the register can be found in Table 2. Acupuncture treatment and combined treatment should be recorded at each visit. Changes in symptoms, ODI, and NRS scores were recorded before and after treatment for effectiveness evaluation.

**Table 2 Tab2:** Timetable for data collection

Data elements	Therapeutic Session					Follow-up Period			
	Minimum treatment^a^			…	Last Visit	Minimum follow-up^b^			…
	First Visit	Second Visit	Thirdly Visit			Week 1	Week 12	Week 24	
Demographic information	✓								

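### Table 2 schedules NRS and ODI follow-up at weeks 1, 12 and 24, while the abstract, participant timeline and analysis section use weeks 1, 4 and 12

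*Protocol article*

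**What the plan says.** Three places in the protocol article give one follow-up schedule:

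- The abstract (Methods) has the evaluation measures collected at baseline and at "follow-up in 1, 4, 12 weeks after the last visit".
- The Participant timeline section sets the same weeks as a minimum: "At least ensure follow-up at these three time points,1 week, 4 weeks and 12 weeks".
- The Analytic approach section takes them as the analysis time points: "We will select 1-week,4-week,12-week, assessments respectively at evaluation time point on the ODI and NRS index". Its model for predictors also stops at week 12: "predictors of long-term effectiveness presented by ODI and NRS or recurrence at the12-week follow-up".

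Table 2, under Data elements and collection methods, gives another. Its minimum follow-up columns read "Week 1 Week 12 Week 24", and its footnote asks for "No less than three follow-up visits". The rows "Numerical Rating scale (NRS)" and "Oswestry Disability Index (ODI)" are ticked at the first visit, the last visit and those three follow-up weeks. The text introducing the table says that it holds the register's minimum dataset.

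The Primary outcomes section names NRS and ODI as primary outcomes. The Background says that the study is already recruiting.

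**The concern.** Both schedules stand in the current text and both are put as minimums, yet they differ. A centre that completes weeks 1, 12 and 24 meets Table 2 in full and still misses a follow-up that the Participant timeline requires. A centre that completes weeks 1, 4 and 12 meets the timeline and leaves a Table 2 column empty.

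The week-4 half of the mismatch carries the statistical weight, because a stated analysis of the primary outcomes depends on it. NRS and ODI are self-reports of the patient's state at the time of asking. A score not taken about four weeks after the last visit cannot be obtained afterwards except by recall. Since patients are already being recruited, any loss grows until the text is corrected.

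**Working it through.** No sample size, power or event figure enters this point. The check compares the stated time points, confirms how the table should be read, and asks whether the visit window could reconcile the two schedules.

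**1. Time points side by side**

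| Place in the protocol article | Week 1 | Week 4 | Week 12 | Week 24 |
|---|---|---|---|---|
| Abstract, Methods | yes | yes | yes | no |
| Participant timeline | yes | yes | yes | no |
| Analytic approach | yes | yes | yes | no |
| Table 2, NRS and ODI rows | yes | no | yes | yes |

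Analysis set {1, 4, 12}; Table 2 set {1, 12, 24}.

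- Common to both: {1, 12}.
- Analysed but not tabulated: {4}, one of three analysis time points.
- Tabulated but not in any analysis stated here: {24}, one of three named follow-up visits.

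**2. Is the table read correctly?** Its header has nine columns: first, second and third visit, an open column, last visit, weeks 1, 12 and 24, and a second open column. The NRS and ODI ticks fall in columns 1, 5, 6, 7 and 8, that is, first visit, last visit and weeks 1, 12 and 24. The ticks have not shifted in the conversion from PDF, and the column labels themselves contain no week 4.

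**3. Could the open follow-up column supply week 4?** No. It comes after week 24, and only the disease status row is ticked there. NRS and ODI are not.

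**4. Could the visit window supply week 4?** The Participant timeline allows 3 days around each follow-up point. Counting days from the last visit:

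- Week 1: 7 ± 3 = days 4 to 10.
- Week 4: 28 ± 3 = days 25 to 31.
- Week 12: 84 ± 3 = days 81 to 87.

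The week-1 window closes 25 − 10 = 15 days before the week-4 window opens. The week-12 window opens 81 − 31 = 50 days after it closes. No tabulated visit can stand in for week 4.

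**5. Could multiple imputation supply it?** The Missing data section plans multiple imputation. If collection followed Table 2 throughout, there would be no observed week-4 score on which to base an imputation model. Week-4 values would then come entirely from an assumed course between weeks 1 and 12.

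**The case against.** The strongest reply is that Table 2 is the outlier. Three places agree, the analysis section among them, and the table may simply carry wrong column labels. Data are entered through one central platform, with trained users, an investigator's manual and monthly inspection. If the platform form asks for weeks 1, 4 and 12, nothing has been lost. This stands as a limit on the consequence. It does not remove the contradiction, because the article gives Table 2 operative status and a reader cannot tell which schedule was intended.

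Four stronger readings are tempting, and the documents do not support them:

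- *Week 4 is not collected at all.* This is true of Table 2 only. The abstract and the Participant timeline both schedule a week-4 follow-up.
- *Sites work from Table 2, so time points differ by site and missingness is confounded with centre.* The article does not say which document sites work from. With one shared platform, an error in the form would more likely affect all centres alike.
- *Week 4 is 100% missing, against the plan's 20% ceiling.* The first figure assumes that Table 2 is followed. The second is a target set in a paragraph on follow-up nonresponse, and a visit that was never scheduled is a different matter.
- *The week-24 data are wasted.* A registry may collect more than one analysis uses, and an analysis plan that is not shown may use week 24. All that can be said is that this document states no analysis of it.

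Describing a 12-week result as long-term is loose labelling without statistical consequence. Whether one time point should be the main comparison is a separate question that this contradiction does not settle.

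**Conclusion.** The contradiction is certain. It lies in explicit current text and is not explained by PDF conversion, by black-outs or by the shortening of a full protocol into an article. It concerns the primary outcomes: the two schedules agree on two of three follow-up points and differ on the third.

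The consequence rests on one assumption that cannot be checked from the article, namely which schedule the platform form uses. If it uses Table 2, the planned week-4 analysis of NRS and ODI has no data, and the loss is permanent for every patient already past that window. If it uses weeks 1, 4 and 12, no stated analysis suffers and only the table needs correcting. As written, the plan allows either. It should be corrected before more follow-up accrues.

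**What to change.** 1. Reconcile the abstract, Participant timeline, Table 2 and Analytic approach to one set of follow-up time points, so that every time point analysed is a column in Table 2 with NRS and ODI ticked.
2. Check that the platform form carries the same set.
3. Notify sites of the agreed schedule.
4. If week 24 is kept, state its use: analysed, or collected for description only.

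The cost is a corrected table or text, a check of the platform form (with a change if it does not match) and a note to sites. No additional patients are needed. If the check shows that the form has followed Table 2, week-4 scores already missed stay missing, and the report should say so.
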